### Secondary endpoints

The following secondary endpoints will be examined: 1) successful targeting rates during localization (defined as the number of successful targeting procedures divided by the number of all localization procedures); 2) successful targeting rates in the operating field (defined as the number of successful targeting procedures minus the number of wire dislodgements or dye fading/spillage occurring in the operation field divided by the number of all localization procedures); 3) time at risk (defined as the time elapsed between the completion of localization and skin incision); 4) other time parameters (including operating time, length of time under anesthesia, global operation room utilization time, and length of hospital stay); 5) rate of conversion to thoracotomy; and 6) complication rates. The occurrence of complications (including pneumothorax and lung hemorrhage) will be recorded after the initial follow-up CT scan following localization. According to the 2010 British Thoracic Society guidelines, large or small pneumothorax will be defined by a distance between the lung margin and chest wall greater or less than 2 cm, respectively [21]. As far as radiation doses are concerned, we will quantify the radiation dose delivered to patients by determining the effective dose (ED). During POCT procedures, the radiation dose delivered by MDCT will be determined using the dose length product (DLP) and expressed as mGy/cm. The radiation dose will be converted to the ED using a suitable conversion factor (0.014, mSvGy^− 1^ cm^− 1^) [22]. During IOCT procedures, the radiation doses delivered by both CBCT and fluoroscopy will be determined using the dose area product (DAP) and expressed as mGy/cm^2^. Two appropriate conversion factors (0.146 and 0.12 mSvGy^− 1^ cm^− 2^) will be used to calculate the ED for CBCT and fluoroscopy, respectively [23, 24]. Four sets of thermoluminescent dosimeters (TLDs; UD-802A; Panasonic, Osaka, Japan) will be also placed around the patient’s chest wall (in proximity to the lesion of interest). The radiation dose absorbed by each TLD will be measured using a TLD reader (UD-716AGL TLD reader; Panasonic, Tokyo, Japan) and mean values will be used for analysis.

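### The effective-dose conversion is stated in units that do not yield mSv in either arm, and the base (per Gy or per mGy) of each factor needs confirming before the arms are compared

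*Protocol article*

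**What the plan says.** The protocol article, under Secondary endpoints, makes effective dose the measure of patient radiation: "we will quantify the radiation dose delivered to patients by determining the effective dose (ED").

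- **POCT arm.** "the radiation dose delivered by MDCT will be determined using the dose length product (DLP) and expressed as mGy/cm". The next step is "The radiation dose will be converted to the ED using a suitable conversion factor (0.014, mSvGy" with exponents that make it mSv Gy⁻¹ cm⁻¹.
- **IOCT arm.** The doses from cone-beam CT and from fluoroscopy "will be determined using the dose area product (DAP) and expressed as mGy/cm", with a superscript 2 on the cm. Then: "Two appropriate conversion factors (0.146 and 0.12 mSvGy" with exponents that make them mSv Gy⁻¹ cm⁻², the first for cone-beam CT and the second for fluoroscopy.

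The article refers to cited sources for the factors. It gives no expected dose length product (DLP), dose area product (DAP) or effective dose, and no mGy-to-Gy step.

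**The concern.** A DLP is dose times length and a DAP is dose times area. The article writes both as dose divided by length or area, then multiplies by factors whose units fit only the product form. It also records in mGy and converts with factors per Gy. An analyst who follows the paragraph has to guess twice: what the slash means, and whether to divide by 1000.

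Radiation exposure is a listed secondary outcome and the safety issue that the Discussion singles out. Effective dose is the only radiation measure with a conversion set out for each arm. The check of case record forms against source records (Data collection and management) would not catch a conversion error, because the raw readings would agree and the error would enter afterwards. If the guess came out differently for the two arms, or if the factors do not share a base, the size of the between-arm difference would be set by a unit slip.

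**Working it through.** There is no effective dose in the article to reproduce, so the check is of units first and scale second.

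**Inputs from Secondary endpoints.** DLP in mGy/cm with k = 0.014 mSv Gy⁻¹ cm⁻¹. DAP in mGy/cm² with k = 0.146 (cone-beam CT) and 0.12 (fluoroscopy) mSv Gy⁻¹ cm⁻².

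**1. Units as written**

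- POCT: (mGy cm⁻¹) × (mSv Gy⁻¹ cm⁻¹) = 10⁻³ mSv cm⁻²
- IOCT: (mGy cm⁻²) × (mSv Gy⁻¹ cm⁻²) = 10⁻³ mSv cm⁻⁴

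Neither is mSv.

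**2. Units with the slash read as a product**

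- POCT: (mGy cm) × (mSv Gy⁻¹ cm⁻¹) = 10⁻³ mSv
- IOCT: (mGy cm²) × (mSv Gy⁻¹ cm⁻²) = 10⁻³ mSv

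The length units now cancel. The factor of 1000 remains and is the same in both arms. Dividing by 1000 in both arms, or in neither, leaves the IOCT/POCT ratio unchanged; omitting it makes both absolute doses 1000 times too large.

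**3. Can the factors share a base?** For one uniform exposure of width W, DAP is roughly DLP × W. The two routes then give the same effective dose when W = k(DLP) / k(DAP).

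- All factors per Gy, as printed: 0.014/0.146 = 0.096 cm; 0.014/0.12 = 0.117 cm. This is a field about 1 mm wide.
- If 0.014 were per mGy·cm, that is 14 per Gy·cm: 14/0.146 = 96 cm; 14/0.12 = 117 cm.

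Take W between 10 and 40 cm (an assumption). With a shared base, the DAP route exceeds the DLP route for the same exposure by a factor between 10 × 0.12/0.014 = 86 and 40 × 0.146/0.014 = 417. With the mixed base, the factor is between 0.086 and 0.417. The check is good only to an order of magnitude, since DLP and DAP refer dose to different points, and neither reading agrees exactly. The shared base is further off.

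**4. Illustration with assumed readings.** None of these readings is in the article: DLP 100 to 1,000 mGy·cm; DAP 5,000 to 50,000 mGy·cm², all treated as cone-beam CT.

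| Treatment | POCT (mSv) | IOCT (mSv) | IOCT/POCT |
|---|---|---|---|
| mGy number × factor, both arms | 1.4 to 14 | 730 to 7,300 | 52 to 5,200 |
| Converted to Gy, both arms | 0.0014 to 0.014 | 0.73 to 7.3 | 52 to 5,200 |
| 0.014 per mGy, 0.146 per Gy | 1.4 to 14 | 0.73 to 7.3 | 0.05 to 5.2 |

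The ratio limits are 730/14 = 52 and 7,300/1.4 = 5,214 in the first two rows, and 0.73/14 = 0.052 and 7.3/1.4 = 5.2 in the third. The first two rows differ by 1000 in absolute dose but not in ratio. The third differs from both by exactly 1000 in ratio. In the first two rows the arms do not overlap at all; in the third they do.

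**The case against.** The strongest reply is that this is a typesetting slip. The text itself calls each quantity a product, there is a stray comma after 0.014, and a radiation physicist would read the intended units without difficulty. The printed mismatch is also symmetric, so it cannot by itself bias the comparison. The endpoint is secondary. The Discussion already warns that the dose figures reported by the two kinds of scanner compare poorly, and adds dosimeters to measure surface dose.

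Much of this stands. The symmetry is correct, and nothing here touches randomization, sample size or the primary outcome of localization time. The dosimeters are a weaker answer: the Discussion describes them for IOCT patients only, so they do not clearly supply a between-arm comparison. A slip in notation also still has to be put right where the text is the conversion rule itself.

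A reader might go further and infer that one arm's effective dose is certain to be about 1000-fold off and the radiation comparison invalid. The document does not support that. It requires 0.014 to be a per-mGy factor while the other two are per Gy, and the article prints all three per Gy. The sources that would settle it are not available here. The field-width check and the assumed readings make a mixed base plausible, but they rest on inputs the article does not give. Likewise, any single figure for the ratio, such as 700-fold, reflects the readings chosen.

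**Conclusion.** The point holds for the units and, as a risk, for the comparison.

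- **Certain from the text:** in both arms the dose quantity is written as a quotient, and mGy readings are paired with per-Gy factors. The rule as stated does not produce mSv in either arm.
- **Not established:** that the factors have different bases. Their relative size suggests it. If it is so and both arms are treated alike, the IOCT/POCT ratio is off by 1000; if only one of the two IOCT factors differs, the error is smaller and depends on that component's share of the dose. Hence up to 1000-fold.
- **If the bases are in fact the same,** the ratio is unaffected provided both arms are converted consistently, and only the absolute doses are at risk.

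Severity is moderate. The outcome is a secondary safety endpoint, and effective dose can be recomputed from the recorded DLP and DAP at any time before reporting.

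**What to change.** In Secondary endpoints, and in the analysis code:

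1. Write DLP as mGy·cm and DAP as mGy·cm² (or Gy·cm²).
2. Before analysis, look up each of the three factors in its cited source and print it with its confirmed base, per Gy or per mGy.
3. State where the division by 1000 is applied, if it is, so that each arm's effective dose comes out in mSv.
4. Add one worked example per arm, from a console reading to mSv with separate cone-beam CT and fluoroscopy terms for IOCT, and use it as a range check on the computed values.

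The cost is one corrected paragraph, a look at the cited sources and a few lines of code. No new data are needed, and no patient already enrolled is affected.

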### Follow-up schedule

The start of the study will be set at randomization. Follow-up will be performed until 3 months after surgery according to a predetermined schedule (Fig. 4). Within one week of the operation, we will assess the primary study endpoint. The following variables will be collected: postoperative complications, readmission rates, and deaths occurring within 30 and 90 postoperative days. Postoperative visits will be scheduled at 3–4 weeks after surgery and at 3 postoperative months.

**Fig. 4 Fig4:**
[figure not shown]
Schedule of patient enrolment, interventions, and assessments; Standard Protocol Items: Recommendations for Interventional Trials (SPIRIT)

### Sample size calculation

The sample size was established according to a retrospective study previously designed by our group [25]. Our original assumption was that the time required for tumor localization would be the same in the IOCT and POCT groups. Based on a two-sample *t*-test under an equality hypothesis, at least 24 patients per treatment arm will be required under the following conditions: alpha error, 0.05; power, 80%; and a balanced trial design. Under the assumption of a 10% total dropout rate, we are planning to enroll at least 27 patients in each arm.

### Timeline

The clinical trial will last two years, a time span that includes prearrangement and statistical analysis. Recruitment began on October 8, 2018, with a planned 2-year duration. Data analysis is scheduled to start upon discharge of the last randomized patient.

## Discussion

Currently, two major techniques can be implemented for performing CT-guided VATS removal of pulmonary nodules. The first is a two-stage approach based on preoperative lesion localization in a CT suite followed by its excision in an operating room, whereas the second consists in single-stage localization and removal in a hybrid OR.

It is a common assumption that IOCT-guided VATS performed in a hybrid OR may ultimately reduce the time at risk between localization and the subsequent excision when compared to POCT—ultimately resulting in a more patient-centered approach. The current randomized clinical trial will be the first to test the hypothesis that, besides reducing the time at risk, IOCT-guided VATS could also be as effective as the conventional two-stage POCT-guided approach for localizing pulmonary nodules. In particular, we will focus on the time required for localization when each approach will be used (a variable which will serve as the primary study endpoint). In addition, we will compare the successful targeting rates during surgery. In terms of safety, a point that will merit consideration is the radiation exposure delivered to patients. Because CBCT and MDCT differ significantly in terms of radiation dynamics, direct use of scanner-estimated doses will be suboptimal for comparison purposes. In order to circumvent this issue, patients in the IOCT arm will be requested to apply TLDs. This approach will allow obtaining direct measures of individual surface radiation exposure. Finally, we are aware that the utilization of the IOCT-guided approach in a hybrid OR may potentially increase the procedural costs (owing to a longer time under anesthesia and a higher global OR utilization time). The question as to whether IOCT will be cost-effective compared with POCT will be assessed separately.

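### Dosimeters are introduced to make radiation dose comparable between arms, but the article names only the IOCT arm for them and elsewhere leaves the arm unstated

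*Protocol article*

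**What the plan says.** The abstract lists radiation exposure among the secondary endpoints, and the Background names it as one of four aspects on which the two techniques will be investigated.

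The Secondary endpoints section gives each arm an effective dose by its own route:

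- **POCT:** "During POCT procedures, the radiation dose delivered by MDCT will be determined using the dose length product (DLP"), then converted with a factor of 0.014.
- **IOCT:** "the radiation doses delivered by both CBCT and fluoroscopy will be determined using the dose area product (DAP"), then converted with 0.146 for CBCT and 0.12 for fluoroscopy.

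Directly after the IOCT text, the same section adds that four sets of TLDs "will be also placed around the patient’s chest wall (in proximity to the lesion of interest"). It names no arm. On how the readings are used, it says that "mean values will be used for analysis".

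The Discussion gives the reason for the dosimeters. Because CBCT and MDCT behave differently, "direct use of scanner-estimated doses will be suboptimal for comparison purposes". To get round this, "patients in the IOCT arm will be requested to apply TLDs", and "This approach will allow obtaining direct measures of individual surface radiation exposure". This is the only sentence that links TLDs to an arm. The description of POCT-guided localization does not mention dosimeters.

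**The concern.** CBCT is the IOCT device and MDCT is the POCT device, so the comparability problem raised in the Discussion is a problem of comparing the two arms. A measurement introduced to solve it has to be taken in both. The only arm named is IOCT, and the methods text neither confirms nor corrects that.

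A study team that follows the Discussion literally would collect surface dose in IOCT alone. The trial could then report how much surface dose IOCT patients receive, but not whether it is more or less than in POCT. Radiation is the safety topic the Discussion singles out, and a reading not taken during a procedure cannot be recovered at analysis.

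**Working it through.** **1. The sections side by side**

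| Place in the article | Dose measure | POCT | IOCT |
|---|---|---|---|
| Secondary endpoints | Effective dose from scanner output | DLP × 0.014 | DAP × 0.146 (CBCT), DAP × 0.12 (fluoroscopy) |
| Secondary endpoints | TLD surface dose, mean of readings | not stated | not stated (sentence follows the IOCT text) |
| POCT-guided localization | TLD | not mentioned | – |
| Discussion | TLD surface dose | not mentioned | named |

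**2. Numbers available**

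The Sample size calculation section gives 24 per arm and a 10% dropout rate. Inflating, 24 / (1 − 0.10) = 26.7, rounded up to 27 per arm, which reproduces the planned enrolment.

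- IOCT-only reading: about 24 to 27 patients with TLD data in IOCT and 0 in POCT. No difference in mean TLD dose can be estimated.
- Two-arm reading: about 24 against 24 after dropout.

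**3. What remains under the IOCT-only reading**

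TLD readings in IOCT are surface dose. The POCT figure is effective dose in mSv derived from DLP. These are different quantities and cannot be set against each other. The two-arm contrast left is effective dose against effective dose:

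mean(0.146 × DAP_CBCT + 0.12 × DAP_fluoroscopy) − mean(0.014 × DLP)

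Each factor is used in one arm only. If the right POCT factor were 0.014 × (1 + e), every POCT effective dose would be misstated by the same multiple, 1/(1 + e), and no IOCT dose would change. That shift would look like an arm difference. Randomization does not remove it and a larger sample does not shrink it. The same holds for the two IOCT factors. The article gives no uncertainty for any factor, so the size of e cannot be stated.

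**4. Precision if TLDs are worn in both arms**

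For a difference in means with a common SD and n per arm, the 95% CI half-width in SD units is t(0.975; 2n − 2) × √(2/n).

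- n = 24: 2.013 × √(2/24) = 2.013 × 0.289 = 0.58 SD.

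The article gives no SD for TLD dose, so this cannot be turned into dose units.

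**5. Precision if TLDs are added to POCT part-way**

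This case is illustrative and assumes even accrual over the two years, a change made on the publication date, and no POCT dosimeters before it. From October 8, 2018 to July 4, 2019 is 269 days, and 269/731 = 0.37 of the recruitment period. That leaves 27 × (1 − 0.37) ≈ 17 per arm before dropout.

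- n = 17: 2.037 × √(2/17) = 2.037 × 0.343 = 0.70 SD.

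Dropout or a later change would widen the interval further.

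**The case against.** The best defence is that the article never says POCT patients go without dosimeters. The paragraph in Secondary endpoints opens with dose delivered to patients in general, deals with POCT, then IOCT, and then adds TLDs. That can be read as covering everyone. The contrary sentence sits in the Discussion, and its stated purpose of comparison fits a drafting slip at least as well as a one-arm design. This stands: a reader might infer that TLDs are definitely confined to IOCT, and the text does not establish that. It does not remove the point, because on the two-arm reading the Discussion misdescribes the design and still needs correcting.

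A reader might also infer that POCT has no dose on a scale shared with IOCT. The article does not support that. Both arms get an effective dose in mSv, so a radiation comparison survives. What may be missing in POCT is direct measurement.

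Nor does the article call the converted doses suboptimal. It applies that word to direct use of scanner estimates, and conversion is a step beyond direct use. Still, the converted figures depend on scanner output and on arm-specific factors, so part of the weakness carries over.

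Finally, an article condenses a fuller protocol, which may name the arms. But the difficulty is more than an omission: the article makes a positive statement about one arm that does not serve the purpose it gives.

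**Conclusion.** The point holds as an inconsistency with a conditional consequence. The Discussion assigns to one arm a measurement whose stated purpose needs two, and Secondary endpoints does not settle which arms are meant. If TLDs are used in IOCT only, the between-arm TLD contrast cannot be estimated (up to about 27 patients against 0), and the radiation comparison depends wholly on three conversion factors that are each tied to one arm. If both arms wear TLDs, the fault is one of wording, and a contrast with a half-width of about 0.58 SD is available at 24 per arm, assuming a common SD and complete readings.

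It would go too far to conclude that the trial cannot compare radiation at all, since effective dose is planned in both arms. Radiation exposure is a secondary endpoint. The primary outcome, sample size and allocation are not touched. The point should be addressed and, if POCT patients are being treated without dosimeters, addressed promptly, since each such patient is lost to the TLD comparison.

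**What to change.** First establish which patients have been given TLDs, then reconcile the Discussion and Secondary endpoints sections so that both name the arms.

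- **Preferred:** state that the same four TLD sets are placed at the same positions relative to the lesion in both arms, and that mean TLD dose is compared between arms alongside effective dose.
- **If both arms already wear TLDs:** correct the Discussion sentence and name both arms in Secondary endpoints. Nothing else changes.
- **If POCT patients have been treated without TLDs:** limit the TLD comparison to patients randomized after the change, so that it stays randomized and concurrent. Say in advance that its precision will be lower than with 24 per arm (95% CI half-width above about 0.58 SD; about 0.70 SD in the illustrative case above). Earlier IOCT readings can be reported descriptively.
- **If TLDs stay in IOCT only:** state that the TLD data are descriptive and do not support a between-arm comparison, and that the comparison rests on converted effective dose.

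The cost is dosimeters and readings for up to about 27 more patients, with a reader already in the plan, and a short amendment. The measurement is non-invasive.

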### Trial status

The trial commenced on October 8, 2018 and the recruitment period is projected to last 2 years. Data analysis will be started upon discharge of the last randomized patient.

## Data Availability

Raw data will be available from the corresponding author upon reasonable request. Transfer of clinical data will require approval from the Institutional Review Board.

## Abbreviations

CBCT: Cone-beam computed tomography
CRF: Case record form
CT: Computed tomography
ENB: Electromagnetic navigation bronchoscopy
GCP: Good clinical practice
GGNs: Ground glass nodules
HORs: Hybrid operating rooms
IOCT: Intraoperative computed tomography
OR: Operating room
POCT: Preoperative CT
SPIRIT: Standard Protocol Items: Recommendations for Interventional Trials
TLDs: Thermoluminescent dosimeters
VATS: Video-assisted thoracoscopic surgery
